## ACRONYMS LIST

|         |                                                                                                    |
|---------|----------------------------------------------------------------------------------------------------|
| ALB     | Albendazole                                                                                        |
| APOC    | African Programme for Onchocerciasis Control                                                       |
| CNTD    | Centre for Neglected Tropical Diseases, Liverpool School of Tropical Medicine                      |
| CY      | Calendar Year                                                                                      |
| DFID    | Department for International Development (U.K.)                                                    |
| DSA     | Disease-Specific Assessment                                                                        |
| EOEEAC  | Ethiopia Onchocerciasis Elimination Expert Advisory Committee                                      |
| EPHI    | Ethiopian Public Health Institute                                                                  |
| F and E | Facial Cleanliness and Environmental Improvement (part of the SAFE strategy)                       |
| FMOH    | Federal Ministry of Health                                                                         |
| FPSU    | Filariasis Programmes Support Unit, Liverpool School of Tropical Medicine (formerly known as CNTD) |
| GTMP    | Global Trachoma Mapping Project                                                                    |
| HDA     | Health Development Army                                                                            |
| HEW     | Health Extension Worker                                                                            |
| ICT     | Immunochromatographic Test                                                                         |
| IEC     | Information, Education and Communication                                                           |
| ITI     | International Trachoma Initiative                                                                  |
| IVM     | Ivermectin                                                                                         |
| LF      | Lymphatic Filariasis                                                                               |
| LFTW    | Light For The World                                                                                |
| M&E     | Monitoring and Evaluation                                                                          |
| MDA     | Mass Drug Administration                                                                           |
| MEB     | Mebendazole                                                                                        |
| MMDP    | Morbidity Management and Disability Prevention Program                                             |
| MOH     | Ministry of Health                                                                                 |
| MOU     | Memorandum of Understanding                                                                        |
| NGO     | Nongovernmental Organization                                                                       |
| NTD     | Neglected Tropical Disease                                                                         |
| OEPA    | Onchocerciasis Elimination Program for the Americas                                                |
| OV      | Onchocerciasis                                                                                     |
| PCR     | Polymerase Chain Reaction                                                                          |
| PC      | Preventive Chemotherapy                                                                            |
| PHCU    | Primary Health Care Unit                                                                           |
| PZQ     | Praziquantel                                                                                       |
| REMO    | Rapid Epidemiological Mapping of Onchocerciasis                                                    |
| RHB     | Regional Health Bureau                                                                             |
| RTI     | RTI International                                                                                  |
| SAC     | School-Aged Children                                                                               |
| SAE     | Serious Adverse Events                                                                             |
| SAFE    | Surgery-Antibiotics-Facial cleanliness-Environmental improvements                                  |
| SCH     | Schistosomiasis                                                                                    |
| SCI     | Schistosomiasis Control Initiative                                                                 |
| SNNPR   | Southern Nations, Nationalities, and People's Region                                               |
| STH     | Soil-Transmitted Helminths                                                                         |
| TAS     | Transmission Assessment Survey                                                                     |
| TF      | Trachomatous Inflammation–Follicular                                                               |
| TIPAC   | Tool for Integrated Planning and Costing                                                           |

|       |                                           |
|-------|-------------------------------------------|
| TOT   | Training of Trainers                      |
| TT    | Trachomatous Trichiasis                   |
| UIG   | Ultimate Intervention Goal                |
| USAID | U.S. Agency for International Development |
| WASH  | Water, Sanitation, and Hygiene            |
| WHO   | World Health Organization                 |
| ZTH   | Zithromax®                                |

## ABSTRACT

*Ethiopia has one of the largest burdens of neglected tropical diseases in the world. The Ethiopian Federal Ministry of Health has set 2020 as the year for the elimination of three of these NTDs: blinding trachoma, lymphatic filariasis, and onchocerciasis. The FMOH has also set 2025 for the elimination of soil transmitted helminths as a public health problem within the country. In order to achieve these goals, Ethiopia must address its endemic communities through years of mass drug administration (MDA) of azithromycin for trachoma, ivermectin for onchocerciasis, ivermectin and albendazole for lymphatic filariasis, and either mebendazole or albendazole for soil transmitted helminths. Currently, WHO guidelines do not condone the combination of azithromycin with any of the other aforementioned drugs during MDA, instead requiring two distinct MDAs separated by several days. This requirement has significant cost implications and human resource demands for national programs and requires a greater investment of time for recipient communities in co-endemic woredas. Pharmacokinetic data as well as some small co-implementation studies suggest that triple drug administration of azithromycin, ivermectin and albendazole is safe. This study seeks to establish the safety profile, assess the community acceptance, and weigh the economic advantages of this three-agent MDA through a non-inferiority randomized control trial. Using a cohort event monitoring design which relies upon both passive and active pharmacovigilance, this study will take place in one district in Oromia region. Within this district, the study will target a recipient population of at least 16,000 people. The primary outcome will be to demonstrate the safety of the triple-drug administration as measured by incidence of AEs/SAEs over a one month period following the MDA. Secondary outcomes of the study will include a qualitative analysis of the perceptions of the beneficiaries receiving the co-administration especially surrounding pill burden and the change in MDA distribution schedule; a qualitative analysis of the perceptions of the co-administration strategy by the local health workforce as a means of PC-NTD drug delivery; a cost analysis comparing existing MDA unit costs from woredas within the regions already on a standard MDA schedule with that of the co-administered woredas; and a literature/data review across 19 different countries including Ethiopia which will analyse the possible benefits of co-administration from an economic and epidemiological standpoint when compared with current trends towards achieving 2020 NTD control and elimination goals on a global scale.*

## STUDY PROTOCOL SUMMARY

| History of revision |            |                                                                     |
|---------------------|------------|---------------------------------------------------------------------|
| 1                   | 5/16/2018  | Conditionally approved by LSHTM, waiting the approval from Ethiopia |
| 2                   | 09/08/2018 | Approved by AHRI/ALERT Ethics Committee                             |

|                    |                                                                                                                                                                                                                                                                                                                                                                                                                                                                                                                                                                                                                                                                                                                                                                                                              |
|--------------------|--------------------------------------------------------------------------------------------------------------------------------------------------------------------------------------------------------------------------------------------------------------------------------------------------------------------------------------------------------------------------------------------------------------------------------------------------------------------------------------------------------------------------------------------------------------------------------------------------------------------------------------------------------------------------------------------------------------------------------------------------------------------------------------------------------------|
| Title              | Safety of the co-administration of azithromycin, albendazole and ivermectin versus standard treatment regimens during mass drug administration (MDA) in Ethiopia: a cluster-randomized trial                                                                                                                                                                                                                                                                                                                                                                                                                                                                                                                                                                                                                 |
| Objective          | To establish the safety profile, assess the community acceptance, and weigh the economic advantages of a three-agent MDA combining azithromycin, albendazole (Alb), and ivermectin (Ivm) in comparison to the standard MDA regimen which separates the administration of azithromycin from the dually administered ivermectin and albendazole by a period of two weeks.                                                                                                                                                                                                                                                                                                                                                                                                                                      |
| Design             | A cluster-randomized non-inferiority trial to assess the safety, local acceptance, and economic advantages of combined MDA with azithromycin, albendazole, and ivermectin in one district in Oromia, Ethiopia. Within this district, a study group of 8,000 people will receive the triple drug co-administration. A control group of 8,000 people within the same district will receive the standard MDA treatment beginning with Ivm/Alb followed two weeks later with azithromycin. The study will randomly sort sub-district communities ( Gotes ) into the trial arm and the control arm. The study will compare the “baseline” of adverse events (AEs) and severe adverse events (SAEs) between the two arms to determine if the triple drug therapy is not inferior to the standard treatment. |
| Study Duration     | 6 months                                                                                                                                                                                                                                                                                                                                                                                                                                                                                                                                                                                                                                                                                                                                                                                                     |
| Interventions      | All residents of the selected communities will be invited to participate in the co-administered drug treatment strategy. Consenting/assenting residents of the villages will be screened as per the inclusion and exclusion criteria. Dosage and treatment age groups will follow WHO protocols for lymphatic filariasis, onchocerciasis, STH,  and trachoma  . Study enrolment will continue until the sample size is attained.                                                                                                                                                                                                                                                                                                                                                     |
| Number of subjects | A total of 16,000 people: 8,000 people in the trial arm and 8,000 in the study arm. If there is no increase in adverse events in the trial arm, triple-drug therapy will be used to treat the remaining 4-5,000 people in the district.                                                                                                                                                                                                                                                                                                                                                                                                                                                                                                                                                                      |
| Population         | All individuals living in the selected communities who agree to participate. See below for more information on exclusion criteria.                                                                                                                                                                                                                                                                                                                                                                                                                                                                                                                                                                                                                                                                           |

 WHO: Preventive chemotherapy in human helminthiasis

[http://apps.who.int/iris/bitstream/I0665/43545/1/9241547103\\_eng.pdf](http://apps.who.int/iris/bitstream/I0665/43545/1/9241547103_eng.pdf)

 WHO: Trachoma Control- A guide for trachoma program managers

[http://apps.who.int/iris/bitstream/10665/43405/1/9241546905\\_eng.pdf](http://apps.who.int/iris/bitstream/10665/43405/1/9241546905_eng.pdf)

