## **6. Description of the Study Area**

The directly observed MDA by co-administration of azithromycin, IVM and ALB will take place within the woreda of Kofele in the West Arsi Zone of Oromia in region. This woreda has an estimated population of people. Within this population, the study requires a total of 13,680 individuals with 6,840 in each arm. The study will target a population of 16,000 people which will allow a 15% cushion to factor in non-compliance and exclusionary criteria among the recipients. This woreda was selected due to the co-endemicity of LF and trachoma.

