### **6.1. Kofele woreda**

#### **6.1.1. General information**

Kofele is one of 17 woredas in West Arsi Zone in Oromia region of Ethiopia. West Arsi is bordered on the south by the Sidama Region and the SNNPR, on the west by the SNNPR, on the northwest by East Shewa Zone, on the northeast by the Arsi Zone, and on the east by Bale Zone, and on the Southeast by Guji zone. The administrative center of the zone is in Shashemane. Kofele woreda is 27 KMs southeast from Shashemane, at an elevation of 2695 meters above sea level. Based on the 2014 E.C. estimate by FMOH the woreda has a population of 251,098.

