**On Day 17, 18**, the clinical nurses and HEW from each of the original four teams will perform one last house to house follow up of all the households that received the triple drug administration. (400 HH x 4 teams = 1600 HH) This will be the last active follow-up step.

**Day 19-30**, the HEWs will maintain the reporting form for another two weeks in the event of any additional complaints from the targeted beneficiaries. This will be completely passive and the HEW will only log complaints if they are reported by a beneficiary. On Day 30, all of the co-administration registers and forms will be collected for data analysis from the HEWs.

Note that in the “standard MDA” control arm, the process described above will be conducted twice. First, IVM/ALB MDA will take place for with 14 days of active surveillance then the Trachoma MDA will take place for 14 days of active surveillance. Passive surveillance will continue in the control arm for two weeks after that.

Once the 45th day of the study is reached in Oromia, the field implementation portion of the study will be complete. The DSMB will review the final data before making a recommendation on how the remainder of the population in the woreda should be treated. Should the DSMB and the FMOH agree, the remaining 4-5000 beneficiaries within Homesha will be targeted for co-administration. However, at this juncture, the RCT will be over. The study will move to strictly observational with the same enhanced supervision in place.

Table 3: Follow up Schedule for both the Trial and the Control Arms of the Study

|                                                    | Day 1 | Day 2 | Day 3 | Day 4 | Day 5 | Day 6 | Day 7 | Day 8 | Day 9 | Day 10 | Day 11 | Day 12 | Day 13 | Day 14 | Day 15 | Day 16 | Day 17 | Day 18 | Day 19-30 | Day 31 |
|----------------------------------------------------|-------|-------|-------|-------|-------|-------|-------|-------|-------|--------|--------|--------|--------|--------|--------|--------|--------|--------|-----------|--------|
| Actual Distribution                                |       |       |       |       |       |       |       |       |       |        |        |        |        |        |        |        |        |        |           |        |

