\* Study team will return to each health post at 1 month after the MDA to collect information on reported AE/SAEs

Data will be entered in STATA. All variables will be summarized using descriptive statistics as is appropriate. The co-administration safety will be characterized as safe or unsafe.

Parameters to be determined are:

- Population of study kebeles: composition by age group and sex.
- Prevalence and incidence of adverse events by age group, sex, and kebele
- Severity of adverse events in each kebele
- Average age of participant experiencing adverse events

The null hypothesis is that the occurrence of adverse events will be significantly higher in the co-administration trial communities in comparison to the standard MDA control communities. The study will report the proportion of individuals in each arm experiencing an AE adjusting for

clustering. It will also report the proportion of AEs stratified by age group. The test statistic will be clustered logistic regression using the covariates of severity and treatment package.

It is important to note that we consider that if the number of adverse events in the co-administration arm was markedly higher than in separate administration arms, for example >5% absolute difference in AEs, then the increased number of adverse events would likely outweigh any logistic or cost benefits. However, a stricter non-inferiority margin of 1.5% was used as the basis for the sample size calculation and was selected for two reasons:

- 1) If the trial results in non-inferiority at this level the study believes this represents unequivocal evidence in favour of co-administration; i.e given the absence of a marked increase in adverse events, the logistic and financial advantages mean the rationale in favour of co-administration is clear.
- 2) To provide a more precise estimate of the difference in the proportion of adverse events in the control and intervention arms.

If the trial were not to meet this non-inferiority margin (i.e the upper limit of the 95% CI crossed our specified delta of 1.5%) but did not cross the threshold at which the increase in the number of AEs was clearly unacceptable (5% difference) then the study believes that plausibly co-administration might still be favourable even accepting that it did result in more adverse events were the logistic and financial benefits to be marked.

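### The post-trial roll-out is described as 4-5,000 people, but about 235,000 residents of the study district lie outside the trial, and its trigger is not the criterion the trial tests

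*Protocol*

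**What the plan says.** **Size and place.** The summary (Number of subjects) states of the study district: "If there is no increase in adverse events in the trial arm, triple-drug therapy will be used to treat the remaining 4-5,000 people". Section 8.8 says that, if the DSMB and the ministry agree, "the remaining 4-5000 beneficiaries within Homesha will be targeted for co-administration". Section 6 says the trial "will take place within the woreda of Kofele in the West Arsi Zone of Oromia". Section 6.1.1 gives the size: "Based on the 2014 E.C. estimate by FMOH the woreda has a population of 251,098". Section 6 also sets enrolment: "The study will target a population of 16,000 people which will allow a 15% cushion". Apart from the roll-out sentence in 8.8, Homesha appears only in the table of contents.

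**Trigger.** The protocol describes the basis for the roll-out, or for accepting the regimen, in several ways:

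- The summary requires no increase in adverse events in the trial arm.
- Sections 8.1 and 8.9 accept an excess of up to 1.5 percentage points (7% to 8.5%), judged by the upper limit of the 95% confidence interval.
- Section 8.8 says: "The DSMB will review the final data before making a recommendation on how the remainder of the population in the woreda should be treated". It gives no number and adds ministry agreement.
- Section 8.5 and the DSMB charter (Appendix 10) set a Day 31 review on whether the rest of the district can safely receive triple therapy. They also call the DSMB together if mild or moderate event rates differ significantly between arms. Neither refers to the 1.5-point margin.

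**The concern.** The roll-out is the immediate decision that the trial result feeds. Ethics committees and the DSMB need to know how many people it covers, where they live, and what result would support it. As written, someone who reads the summary pictures a small mop-up of 4-5,000 people. Someone who reads section 6.1.1 alongside the references to the remainder of the district pictures a population some 50 times larger. Section 8.8 also says the same enhanced supervision stays in place, and that commitment means something quite different at the two scales.

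On the trigger, a literal no-increase rule and a 1.5-point non-inferiority rule can give opposite answers from the same data. If the protocol does not say which one informs the DSMB recommendation, the choice could be made after the result is known.

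**Working it through.** **1. The plan's own sample size, to establish what the trial tests.** Inputs from section 8.1 and Table 2: 7% event rate, margin 1.5 points, 90% power, two-sided 95% interval, 190 people per gote, 6-8% between clusters. Assumption: 6-8% is the 95% range of cluster rates, so SD = 0.01/1.96 = 0.0051.

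Gotes per arm = 1 + (1.96 + 1.2816)² × [2 × 0.07 × 0.93/190 + 2 × 0.0051²] / 0.015² = 1 + 34.4 = 35.4, rounded up to **36**.

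36 × 190 × 2 = **13,680**, which matches section 6: "the study requires a total of 13,680 individuals with 6,840 in each arm". With the 15% cushion, 13,680/0.85 = 16,095 (rounded up), consistent with 16,000. So the trial is sized for the 1.5-point margin with equal true rates.

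**2. The remaining population.**

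- Outside the trial: 251,098 − 16,000 = **235,098** (or 251,098 − 13,680 = 237,418 if only the required number enrol).
- Ratio to the stated figure: 235,098/5,000 = 47.0 and 235,098/4,000 = 58.8.
- District size implied by the roll-out text: 16,000 + 4,000 to 16,000 + 5,000 = 20,000-21,000, which is 8.0-8.4% of 251,098.
- Eligibility: section 7.2 excludes children under 5 and pregnant and lactating women, among others. The protocol gives no eligible share. Assuming 60-85%: 0.60 × 235,098 = 141,059 and 0.85 × 235,098 = 199,833. The smallest ratio is 141,059/5,000 = 28.

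**3. Whether the two triggers can disagree.** Use the same SD, equal true rates of 7%, and first read no increase as an observed difference at or below zero (a second assumption).

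SE = √[2 × (0.07 × 0.93/190 + SD²)/gotes per arm]. Non-inferiority is met when the observed excess is below 1.5 − 1.96 × SE. Its probability under equality is Φ(1.5/SE − 1.96), with SE in points. Subtracting 0.5 gives the chance that it is met with a higher observed rate in the trial arm.

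| Gotes per arm | SE (points) | Largest excess still non-inferior | Non-inferiority met | Met with a higher observed trial-arm rate |
|---|---|---|---|---|
| 36 | 0.45 | 0.61 | 91% | 41% |
| 42 | 0.42 | 0.68 | 95% | 45% |

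With a larger between-cluster SD of 0.01, the last two columns become 86% and 36% (36 gotes) or 90% and 40% (42 gotes).

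**4. A softer reading.** If no increase means no statistically significant increase at the trial's 95% level, the limit on the observed excess is 1.96 × SE, or 0.89 points with 36 gotes and 0.82 with 42. This rule is then the looser of the two. Under equality it is met 97.5% of the time, so the rules disagree in 97.5 − 91.2 = 6.3% of trials with 36 gotes and 97.5 − 94.7 = 2.8% with 42. They disagree less often, and in the opposite direction.

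**The case against.** The strongest reply is that the summary line is shorthand. The Design row of the same summary says the comparison is to determine whether triple therapy is not inferior, so no increase may simply mean non-inferior. That is a fair reading, and it would remove the conflict with the margin. But the line does not say so, and the operative sections (8.5, 8.8 and the charter) do not name the margin either. The point about inconsistent wording stands. The 41-45% depends on the literal reading and should be quoted only with that condition.

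The figure of 4-5,000 could also be a deliberate limit, or text left over from another site. Either may be true, and the second would explain the place name. Neither is stated, and neither makes Homesha part of Kofele.

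Four stronger readings are tempting but unsupported:

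- *Section 8.9 lets the roll-out rule be bypassed.* That section does say "the study believes that plausibly co-administration might still be favourable" for results between 1.5 and 5 points. But it makes this conditional on marked logistic and financial benefits, and it never mentions treating the rest of the district. It concerns how the result is interpreted.
- *The sponsor intends to treat 235,000 people.* No passage says so. The only numbers given for the roll-out are 4-5,000.
- *The roll-out would take about 196 days.* That is 235,098/(8 × 300) × 2 and assumes that the eight trial teams and the two-day cycle continue. Section 8.8 carries over the supervision and says nothing of staffing or pace.
- *The trial result is compromised.* Section 8.8 says the randomised trial is over before the roll-out begins. Randomisation, power and the non-inferiority test are untouched.

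**Conclusion.** The point holds as a wrong stated figure and place, together with an inconsistent decision rule for the observational phase after the trial. The conflict in number and district rests on the text and one subtraction: 235,098 residents outside the trial against 4,000-5,000 stated, a factor of 47 to 59. That is a count of all residents. For people eligible for all three drugs the factor is at least 28, if at least 60% are eligible.

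The conflict over the trigger is also visible in the text. How often it would change the decision depends on assumptions. It is about 41-45% of trials under equal true rates on the literal reading, with 6-8% taken as the 95% range of cluster rates and 36-42 gotes per arm. It is about 3-6% if no increase means no significant increase. This should be corrected before the DSMB is asked for a recommendation, but it does not threaten the primary comparison.

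**What to change.** 1. In the summary and section 8.8, correct the district and restate how many people the roll-out covers, saying whether the count is of residents or of those eligible for all three drugs. If 4-5,000 is meant as a cap, say so and say who falls under it.
2. In section 8.8, state whether the same enhanced supervision applies at the restated scale.
3. Reconcile the roll-out wording in the summary, sections 8.5 and 8.8 and the DSMB charter with the non-inferiority criterion in 8.1 and 8.9, so that one statistical criterion, fixed before results are seen, informs the DSMB recommendation.
4. Notify the ethics committees and the DSMB of the corrected scale and criterion.

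Which rule applies, and how the remaining population is treated, is for the sponsor, the DSMB and the ministry to decide. The cost is text edits in four places plus the notifications, with no change to the sample size, data collection or primary analysis.
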